### 10.2 Secondary study parameter(s)

The reduction in FBF response, due to the administration of caffeine in the presence of dipyridamole and eplerenone, will be analysed in a similar way, using a linear mixed-model analysis with random factor subject, fixed factors dipyramole dose, caffeine (yes/no), dipyramole dose \* caffeine, and period. The logarithm of the baseline FBF will be included as co-variables. The dependent variable will be the log-transformed FBF after eplerenone administration (with and without caffeine). Other endpoints will be analysed using similar random effects models. A p-value of  $< 0.05$  will be considered to be statistically significant.

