On the 7th day of treatment, the vasodilator response to intra-arterial administration of 3 increasing dosages of dipyridamole (10, 30 and 100 ug/min/dL per forearm) will be evaluated, in the absence and presence of intra-arterial infusion of caffeine (90 ug/min per 100 mL of forearm volume). In addition, PORH to 2 incremental periods of forearm ischemia (2 and 5 minutes) will be measured. Forearm ischemia will be induced by inflation of an upper arm cuff to 200 mmHg. During a separate visit (day 8), the vasodilator responses to intra-arterially infused sodium nitroprusside (60 and 600 ng/min/dL) and adenosine (1.5 and 5.0 ug/min/dL) will be determined, to exclude non-specific effects of eplerenone on vascular reactivity and adenosine sensitivity.

Treatment duration of 8 days means administration of eplerenone or placebo twice daily during 7 days and once daily on day 8.

After this first experiment, a wash out period of 4 weeks will avoid any carry-over effect of eplerenone. After these 4 weeks, the participant will be crossed over to receive the alternative treatment arm during 8 days. Again, we will monitor serum on day 3, 4 or 5, and on day 7 and 8 exactly the same experiments will be performed.

The subjects will be studied in supine position after an overnight fast and at least 24 h of caffeine and alcohol abstinence (since caffeine is an adenosine receptor antagonist and alcohol can also affect the adenosine metabolism). Experiments are performed in a temperature-controlled room (24 °C) in the morning after an overnight fast. At the start of the experiment, we will insert a venous cannula into the antecubital vein of the dominant arm for blood drawing. Blood will be drawn before start of each experiment: 20.5 mL on

day 7 for the determination of the serum potassium, sodium, creatinine, plasma caffeine (to check compliance with caffeine abstinence), aldosterone, renin, and eplerenone concentration; and 3 mL on day 8 for the determination of plasma caffeine only. Subjects with a circulating caffeine concentration > 1.0 mg/l will be excluded from analyses. Twenty-four hours urine samples will be collected and sodium and creatinine will be determined, to ensure that salt intake is approximately the same during both treatment days.

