Study medication will be taken under supervision of the researcher. One hour after ingestion of the drug, a 27-gauge needle (B. Braun Medical B.V.) will be inserted into the brachial artery of the non-dominant arm for intra-arterial drug administration. The outer diameter of this needle is 0.4 mm. In both arms, forearm blood flow (FBF) will be measured simultaneously with venous occlusion plethysmography, using mercury-in-silastic-strain gauges and occluded hand circulation as described previously. (12) Thirty minutes after cannulation of the brachial artery, normal saline is infused with concomitant measurement of baseline FBF for 5 min.

So, approximately 1.5 hours after ingestion of the study medication, the experiment will be started and FBF will be measured around the  $T_{\max}$  of eplerenone (approximately 2 hours) Three experiments will be performed, which are all separated by 30 minutes of wash-out.

1. FBF will be measured during the administration of increasing dosages of dipyridamole into the brachial artery. These dosages are similar to a previous study of our group. (10) We hypothesize that in patients treated with eplerenone, the dipyridamole-induced vasodilation is potentiated due to upregulation of CD73.
2. Subsequently, we will measure the vasodilator response to 2 incremental periods of arterial occlusion ('post-occlusive reactive hyperemia'). Forearm ischemia will be induced by inflation of an upper arm cuff to 200 mmHg, as described previously. (11) We have previously demonstrated that the PORH after 2 and 5 minutes of ischemia is potentiated by statins (by increasing the extracellular formation of adenosine) (11) and by dipyridamole (by inhibition of the ENT transporter). (12)

3. We will finish the experiment on day 7 with measurement of FBF during the concomitant administration of the three increasing dosages of dipyridamole and of caffeine (90 ug/min per 100 mL of forearm volume) into the brachial artery.
4. Finally, on day 8, we will record the forearm vasodilator response to the administration of adenosine (1.5 and 5.0 ug/min/dL) and SNP (60 and 600 ng/min/dL) to exclude non-specific effects of eplerenone on vascular function and adenosine sensitivity.

Furthermore, we will measure blood pressure at baseline and during the experiments, on day 7 and 8, in all volunteers.

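### In section 10.2 the caffeine effect is aliased with order: caffeine is always in the third experiment, and the one baseline described comes before the first

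*Protocol*

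**What the plan says.** Protocol section 3 lists three experiments for day 7: "Three experiments will be performed, which are all separated by 30 minutes of wash-out". The first is dipyridamole alone at three doses. The second is reactive hyperaemia: "Subsequently, we will measure the vasodilator response to 2 incremental periods of arterial occlusion". The third adds caffeine: "We will finish the experiment on day 7 with measurement of FBF during the concomitant administration of the three increasing dosages of dipyridamole", together with caffeine. In the second treatment period, "on day 7 and 8 exactly the same experiments will be performed", so the order is neither randomised nor reversed.

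One baseline is described. After cannulation and before the first experiment, "normal saline is infused with concomitant measurement of baseline FBF for 5 min". Flow is recorded in both arms at once, while drugs go only into the non-dominant arm.

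Section 10.2 analyses log FBF after eplerenone, with and without caffeine, in a mixed model with a random subject effect and "fixed factors dipyramole dose, caffeine (yes/no"), their interaction, and period. It adds: "The logarithm of the baseline FBF will be included as co-variables". It has no term for order or time and does not mention the contralateral arm. It describes its target as "The reduction in FBF response, due to the administration of caffeine in the presence of dipyridamole and eplerenone".

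**The concern.** Every caffeine-free value comes from the first dipyridamole series of the session and every caffeine value from the second. In between lie a complete dipyridamole series and two ischaemic periods, which section 1 itself describes as a stimulus to adenosine formation. A drift in resting flow, a residue of the earlier experiments, or a changed response to repeated dipyridamole would all be read as caffeine. A fall would imitate a caffeine effect and a rise would hide one.

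The analysis bears on hypothesis 2 in section 3, that caffeine attenuates the augmented response. A reader would expect the baseline covariate to deal with drift. Whether it can depends on which baseline is meant, and the protocol does not say.

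**Working it through.** **Inputs.** From section 4.4: SD of log FBF 0.35, within-period correlation 0.7, 12 evaluable subjects, two-sided 0.05. From sections 3 and 7.5: three dipyridamole doses of 5 minutes each, 30-minute wash-outs, occlusions of 2 and 5 minutes.

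**The plan's own figure.** Reading the design factor as 1/k + ((k−1)/k)ρ − ρ², with k = 3 and ρ = 0.7, gives 0.333 + 0.467 − 0.490 = 0.31. For ln(1.25) = 0.223 and two groups of 12, the normal approximation gives 80.1% power, which agrees with the stated 80%. The inputs are therefore being read as intended. That figure concerns the primary analysis; the present point does not depend on it.

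**Aliasing.** In the 10.2 data set, caffeine = no occurs only in experiment 1 and caffeine = yes only in experiment 3. The design matrix with columns for intercept, caffeine and order has rank 2 of 3. Period takes one value per subject in eplerenone-only data, so it cannot separate them. A baseline taken once per session is the same number on both sides of each within-subject difference. In simulated complete data, adding it changed the caffeine estimate by less than 1e-15.

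**Time between the series.** From start to start: 15 (three doses) + 30 (wash-out) + 7 (occlusions) + 30 (wash-out) = 82 minutes at least. The first series starts about 1 h 35 min after ingestion, so the caffeine series starts about 3 hours after it.

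**Precision of the stated contrast.** SE = 0.35 × √0.3 × √(2/36) = 0.045.

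**Effect of drift when caffeine does nothing.** The residual degrees of freedom are 72 − 12 − 5 = 55.

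| Assumed order effect | Log scale | Divided by SE | Declared significant |
|---|---|---|---|
| none | 0 | 0 | 5% |
| −5% | −0.051 | 1.14 | 20% |
| −10% | −0.105 | 2.33 | 63% |
| −15% | −0.163 | 3.60 | 94% |

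Simulation of the 10.2 model gives matching rates. In the other direction, a true caffeine reduction of 15% combined with an upward residue of 10% would be estimated as 0.85 × 1.10 = 0.935, a 6.5% reduction.

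**Cost of dividing by each series' own baseline.** SE = 0.35 × √(0.3 × 2 × (1/3 + 1)) / √12 = 0.35 × √0.8 / √12 = 0.090, twice the stated contrast. Power with 11 degrees of freedom:

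| True reduction | SE 0.045 | SE 0.090 |
|---|---|---|
| 15% | 90% | 38% |
| 20% | 99% | 61% |
| 25% | over 99.9% | 82% |

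**Treatment-by-caffeine contrast.** If residuals in the two periods are independent and 12 subjects complete both, SE = √2 × 0.045 = 0.064.

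**The case against.** The strongest reply is that the protocol never says that no further baseline is taken. It describes one at the start of the session, refers to earlier work for the plethysmography and occlusion methods, and uses a plural for baseline FBF in section 10.1. A fresh baseline before each experiment would be compatible with the text, and the choice of covariate could be left to a statistical analysis plan. This stands as far as it goes: that the covariate is useless follows only if the single described baseline is the one used. But a later analysis plan cannot supply a measurement that was not made, and even a fresh baseline would not remove a changed response to repeated dipyridamole.

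Second, the design has safeguards. The 30-minute wash-outs should reduce carry-over, and the contralateral arm can reveal systemic drift. Both count. However, no check that flow returns to baseline is stated, the contralateral arm is not in the 10.2 model, and it would not show a local residue in the infused arm.

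Third, this is a secondary comparison. Section 1 rests the link between dipyridamole and adenosine on earlier studies, so the caffeine result supports that link and is not its only evidence. That is correct and limits the importance of the point.

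Fourth, the ratio to own baseline is costly, as the power table shows. It therefore belongs beside the stated model and should not replace it.

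**Conclusion.** The point holds for the secondary caffeine analysis. As 10.2 is written, caffeine and order are completely aliased, and any order effect passes into the caffeine estimate one for one. That needs no assumed drift size. The rejection rates of 20%, 63% and 94% do: they rest on assumed falls of 5%, 10% and 15%, on the plan's SD and correlation, and on equal correlation among all measurements of a session.

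A reader might infer three stronger things that the protocol does not support:

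- That no baseline is taken before the third experiment. The text is silent on this.
- That drift of this size will occur. No figure is given, and the wash-outs may keep it small.
- That the main result is compromised. The eplerenone-placebo comparison uses the same experiment in the same position in both periods, so order cannot bias it in this way.

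This is an inexpensive improvement that should be made; it is not a fatal flaw.

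**What to change.** 1. In section 3, state that a five-minute saline baseline FBF is recorded immediately before the third experiment, after the 30-minute wash-out and before caffeine starts, in both periods.
2. In section 10.2, say which baseline enters the model. Report the shift in baseline from experiment 1 to experiment 3 with its 95% confidence interval, with contralateral-arm FBF as a check on systemic drift. Give the caffeine effect on log(FBF / own baseline) as a sensitivity analysis beside the stated model.
3. Add the treatment-by-caffeine contrast from both periods. It cancels any order effect common to eplerenone and placebo, and it matches hypothesis 2, which concerns attenuation of the augmented response. It would not cancel a residue that is itself larger under eplerenone.
4. Replace the wording that ascribes the whole difference to caffeine. Say that the within-eplerenone contrast reflects caffeine plus any order effect on the repeated dipyridamole response.

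The order of the experiments need not change. The cost is five minutes of plethysmography per day-7 visit and some rewording. The sensitivity analysis has a standard error of at most about 0.090 against 0.045 under the plan's correlation, and the treatment-by-caffeine contrast about 0.064, so a wide interval from either should not be read as absence of a caffeine effect.

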Measurement of adenosine is extremely difficult (7), because the half life of adenosine in blood is approximately one second, due to rapid uptake and degradation. (8) Therefore,

we have used previously validated and used alternative methods to indirectly study the endogenous adenosine concentration. Dipyridamole increases the extracellular endogenous adenosine concentration by inhibition of the ENT transporter (9) and induces local vasodilation. (10) Therefore, the vasodilator effect of dipyridamole accurately reflects extracellular adenosine formation by the CD73 enzyme. (11)

Our group has recently used this method to demonstrate that statins also augment CD73 activity. Brief arterial occlusion of the forearm is an endogenous stimulus to increase adenosine formation, which subsequently enhances blood flow, resulting in so-called 'post-occlusive reactive hyperemia' (PORH). This effect is also potentiated by dipyridamole and prevented by co-administration of caffeine. (12)

In this research proposal, we aim to investigate in humans in vivo whether eplerenone promotes adenosine receptor stimulation by activating CD73. The results of these studies will provide a possible explanation for the positive effects of MR antagonists on IR-injury.

To test our hypotheses, we will use the vasodilator response in the forearm vascular bed to various stimuli as a well-validated surrogate of adenosine receptor stimulation, as will be explained in more detail in the next section.

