## 3. Study design

In this randomized placebo-controlled double-blinded cross-over study, we will test the following hypotheses:

1. Eplerenone augments the vasodilator response to dipyridamole by activation of CD73
2. The adenosine receptor antagonist caffeine attenuates this augmented vasodilator response to dipyridamole.
3. Eplerenone augments postocclusive reactive hyperemia (PORH)

We chose to use eplerenone over spironolactone, because eplerenone is a selective MR antagonist without binding to the androgen and progesterone receptor, and thus without endocrine side effects. (See also paragraph 6.4 Summary of known and potential risks and benefits)

The design of the study is depicted in figure 1. In brief, we will ask 14 healthy male volunteers (age 18-40 years) to participate. After signing for informed consent, history taking, a physical examination, blood drawing (5 mL for creatinine, potassium, ALAT, total cholesterol and glucose) and electrocardiography will be performed. We would like to refer to paragraph 4.2 and 4.3 for the in-, and exclusion criteria.

After inclusion, the volunteers will be randomly allocated to start receiving either an 8-day treatment with eplerenone or fully mimicking placebo, in a double-blinded design. The

justification of the dose and timing of administration is given in chapter 6. In the first week of treatment (on day 3, 4 or 5 –depending on the weekend-) we will monitor serum potassium by drawing 3 mL of blood, in order to guarantee the safety of treatment with eplerenone. We accept a serum potassium to 5.0 mmol/L (in contrast to 4.7 for inclusion in the study) during the study. In case of a serum potassium of  $\geq 5.1$  mmol/L, the subject will be excluded from the study and the treatment will be stopped. Two days later, serum potassium will be evaluated again.

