#### 8.1.2 Secondary study parameters/endpoints (if applicable)

- Forearm blood flow response to the intrabrachial administration of incremental dosages of dipyridamole, with and without caffeine, after eplerenone treatment.
- Forearm blood flow to incremental periods of arterial occlusion.

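### The caffeine analysis uses only flow measured after eplerenone, so it cannot show that caffeine attenuates the augmentation due to eplerenone (hypothesis 2)

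*Protocol*

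**What the plan says.** Protocol section 3 lists the hypotheses. The first is "Eplerenone augments the vasodilator response to dipyridamole by activation of CD73". The second refers back to it: "The adenosine receptor antagonist caffeine attenuates this augmented vasodilator response to dipyridamole".

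The secondary endpoint in section 8.1.2 is the response to dipyridamole "with and without caffeine, after eplerenone treatment". Section 10.2 models it with subject as random factor and "fixed factors dipyramole dose, caffeine (yes/no"), their interaction and period as fixed factors, with log baseline flow as covariate. The outcome is restricted: "The dependent variable will be the log-transformed FBF after eplerenone administration (with and without caffeine"). There is no treatment factor and no caffeine-by-treatment term. Other endpoints are to be analysed with similar models, but none of those listed is a comparison of the caffeine effect between treatments.

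On conduct, section 3 says of the second period that "on day 7 and 8 exactly the same experiments will be performed", so the dipyridamole-plus-caffeine run is also done under placebo. The order is fixed, with dipyridamole alone first, then the arterial occlusions, then caffeine: "We will finish the experiment on day 7 with measurement of FBF during the concomitant administration".

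**The concern.** Section 1 states that "Dipyridamole increases the extracellular endogenous adenosine concentration by inhibition of the ENT transporter" and that this dilates the forearm vessels. Section 5.2 describes caffeine as an effective blocker of adenosine receptors. Neither statement depends on eplerenone. Caffeine should therefore reduce the dipyridamole response under placebo as well, and a reduction seen under eplerenone alone does not tell us whether the extra response due to eplerenone was touched.

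The fixed order adds a second difficulty. Within the eplerenone period, with caffeine also means last run of the day, so the caffeine effect is mixed with anything that drifts over the session. The period term cannot help, because each subject contributes one period to these data.

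What is at stake is the receptor-blockade check on the dipyridamole result. The adenosine and nitroprusside runs on day 8 address adenosine sensitivity and non-specific vascular effects; the caffeine run is what ties the eplerenone effect to adenosine receptors. As written, it would tend to support that link whether or not the link exists.

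**Working it through.** **Inputs.** From section 4.4: SD of log flow 0.35, within-period correlation 0.7, difference 25% (ln 1.25 = 0.223), 12 evaluable subjects, two-sided 0.05. From section 3: three dipyridamole doses. Assumed, because the protocol gives no figure: the caffeine reduction (10%, 15%, 20%) and any extra run-to-run SD (0 to 0.15).

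**The plan's own figure.** The design factor in section 4.4 is garbled in the text at hand. Read as (1 + (k-1)ρ)/k - ρ² with k = 3, it is 2.4/3 - 0.49 = 0.31. For two groups of 12, 0.223 / (0.35 × √0.31 × √(2/12)) = 2.80, which gives power 80.1% by the normal approximation. The stated 80% reproduces and is not in dispute.

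**The written caffeine test.** Take the mean over three doses with caffeine minus the mean without, within the eplerenone period:

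- variance = 2 × 0.35² × (1 - 0.7) / 3 / 12 = 0.00204, so SE = 0.0452
- with run-to-run SD s: variance = [2 × 0.35² × 0.3/3 + 2s²] / 12

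Probability of a significant result when eplerenone does nothing (noncentral t, 11 df):

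| Run SD | SE | 10% caffeine reduction | 15% | 20% |
|---|---|---|---|---|
| 0 | 0.045 | 57% | 91% | 99% |
| 0.05 | 0.050 | 49% | 85% | 98% |
| 0.10 | 0.061 | 35% | 68% | 92% |
| 0.15 | 0.076 | 24% | 50% | 76% |

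A simulation of 20,000 trials per scenario with no run SD agrees: 57% at 10% and 99% at 20%. The rates are practically the same (56% and 99%) when eplerenone raises flow by 25% and caffeine removes none of that gain. The written test therefore does not separate the two situations.

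**The eplerenone x caffeine contrast.** This is the caffeine effect under eplerenone minus the caffeine effect under placebo. Its SE is 0.0452 × √2 = 0.0639. In the same simulations it is significant in about 5% of trials whenever caffeine leaves the eplerenone gain untouched, whatever the caffeine effect. Power at 10 df:

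| Run SD | Full removal of a 25% augmentation | Half removal |
|---|---|---|
| 0 | 88% | 35% |
| 0.05 | 82% | 30% |
| 0.10 | 65% | 22% |
| 0.15 | 47% | 16% |

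**A limit of this contrast.** Suppose baseline flow 1 and dipyridamole-induced flow 3, total 4. Eplerenone raises the total to 5, all of the gain through adenosine. If caffeine blocks half of the induced flow, the totals become 1 + 2 = 3 and 1 + 1.5 = 2.5, a ratio of 1.20 against 1.25 before. The log interaction is ln(1.25/1.20) = 0.041, with power about 9% at SE 0.0639. At 80% blockade the ratio is 1.8/1.6 = 1.125, the interaction 0.105 and the power about 32%.

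**The case against.** The strongest defence is that hypothesis 2, the endpoint and the model agree on a narrow reading: caffeine lowers the total response measured under eplerenone. The model does estimate that. This stands as a reading, but the answer then does not depend on eplerenone having acted, and so does not serve the mechanistic aim.

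It can also be said that the primary analysis already tests whether eplerenone acts, so a positive caffeine test beside a null primary would mislead nobody. That limits the harm but does not remove it. With a positive primary result, the caffeine test would still be read as confirming the mechanism, and it would be about as likely to be positive if caffeine removed none of the gain.

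Several stronger readings are tempting and the documents do not support them:

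- A reader might infer that the hypothesis requires caffeine to remove the augmentation. The protocol claims attenuation only, so partial removal counts.
- A reader might infer that the test is bound to be positive. That depends on a caffeine effect which the protocol does not state; at 10% with noisy runs the rate is 24%.
- A reader might infer that baseline flow is constant within subject and so cannot adjust the caffeine contrast. Section 3 describes one saline baseline, but section 10.2 does not say which baseline enters for the caffeine run. The period term is uninformative for this contrast, but it is not harmful.
- A reader might infer that the placebo period cancels all order effects. It removes only what is common to both treatments. Residual dipyridamole, for instance, could differ if eplerenone potentiates it, and no passage documents such a residue.

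**Conclusion.** The concern holds. The analysis in section 10.2, with the endpoint in 8.1.2, cannot show that caffeine attenuates the part of the response due to eplerenone, because it has no placebo comparison. With no eplerenone effect, the written test would be positive in about 57% of trials at a 10% caffeine reduction and 99% at 20%, or 24-49% and 76-98% with a run-to-run SD of 0.15 to 0.05. These figures rest on the protocol's SD and correlation, 12 subjects, and an assumed caffeine effect. The qualitative conclusion needs only that caffeine also lowers the dipyridamole response under placebo, which the protocol's rationale implies.

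This should be fixed, but it does not threaten the trial: one secondary analysis is affected. The primary analysis, its stated power and the data collection are untouched.

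**What to change.** Reword sections 10.2 and 8.1.2 before the data are analysed:

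- Include the day-7 dipyridamole runs with and without caffeine from both periods.
- Fixed factors: dose, eplerenone, caffeine, eplerenone x caffeine, and period. Random terms: subject, subject x period, and run within visit.
- Base hypothesis 2 on the eplerenone x caffeine contrast. Report the caffeine effect under each treatment, and the eplerenone effect with and without caffeine, with 95% confidence intervals.
- Keep the eplerenone-only caffeine contrast as descriptive.
- State that a non-significant interaction is not evidence against the mechanism, since on the log scale it can be small when blockade is incomplete.

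The cost is wording only, because the placebo caffeine runs are already planned. The price is precision: the standard error is about 1.4 times that of the eplerenone-only contrast. Power is about 88% for full removal of a 25% augmentation on the protocol's SD and correlation, 47-82% with run-to-run SD 0.15 to 0.05, and about 35% or less for half removal.
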